# Implementation of immunochemical faecal occult blood test in general practice: a study protocol using a cluster-randomised stepped-wedge design

**DOI:** 10.1186/s12885-016-2477-9

**Published:** 2016-07-11

**Keywords:** Colorectal cancer, General practice, iFOBT, FIT, Faecal occult blood test, Early diagnosis, Symptoms, Denmark

## Abstract

**Background:**

Colorectal cancer is a common malignancy and a leading cause of cancer-related death. Half of patients with colorectal cancer initially present with non-specific or vague symptoms. In the need for a safe low-cost test, the immunochemical faecal occult blood test (iFOBT) may be part of the evaluation of such patients in primary care. Currently, Danish general practitioners have limited access to this test. The aim of this article is to describe a study that will assess the uptake and clinical use of iFOBT in general practice. Furthermore, it will investigate the diagnostic value and the clinical implications of using iFOBT in general practice on patients presenting with non-alarm symptoms of colorectal cancer.

**Methods/Design:**

The study uses a cluster-randomised stepped-wedge design and is conducted in the Central Denmark Region among 836 GPs in 381 general practices. The municipalities of the Region and their appertaining general practitioners will be included sequentially in the study during the first 7 months of the 1-year study period. The following intervention has been developed for the study: a mandatory intervention providing all general practitioners with a starting package of 10 iFOBTs, a clinical instruction on iFOBT use in general practice and online information material from the date of inclusion, and an optional intervention consisting of a continuous medical education on colorectal cancer diagnostics and use of iFOBT.

**Discussion:**

This study is among the first and largest trials to investigate the diagnostic use and the clinical value of iFOBT on patients presenting with non-alarm symptoms of colorectal cancer. The findings will be of national and international importance for the future planning of colorectal cancer diagnostics, particularly for ‘low-risk-but-not-no-risk’ patients with non-alarm symptoms of colorectal cancer.

**Trial registration:**

A Trial of the Implementation of iFOBT in General Practice NCT02308384. Date of registration: 26 November 2014

## Background

Colorectal cancer (CRC) is the second most common type of cancer in Denmark and is a leading cause of cancer-related death [1, 2]. In Denmark, approx. 25 % of all new CRC cases in 2013 were diagnosed in stage IV with a 5-year survival of less than 5 % [3]. Considering that CRC is a potentially curable disease when found in earlier stages and that survival is strongly related to stage at diagnosis, these figures underline the importance of increasing the proportion of CRCs diagnosed in early stages.Several initiatives have been made to support a stage shift towards earlier diagnosis of CRC. One important step is screening. Studies show that screening for CRC using faecal occult blood tests may reduce CRC mortality in the screened age group [4–6]. Despite the advantages of screening, 75–80 % of CRC cases must still be found through symptomatic presentation in general practice [7, 8]. Therefore, another important strategy has been to support urgent referral and investigation of patients with CRC alarm symptoms [9–11]. This initiative provides the general practitioner (GP) with the opportunity to refer patients presenting with alarm symptoms of cancer to an urgent colonoscopy. Alarm symptoms include rectal bleeding, change in bowel habits, iron-deficiency anaemia, weight loss and abdominal pain [12]. However, the positive predictive values (PPVs) of alarm symptoms are low (2–8 %). Thus, the GPs must each refer 10–20 patients with alarm symptoms for further diagnostic workup to catch one person with CRC [13–15].

Screening and urgent referral for alarm symptoms are two important improvements of CRC diagnosis. However, 50 % of CRC cases will present in general practice with vague or non-specific symptoms that are not eligible for urgent referral [16]. These symptoms are most often caused by benign conditions and can be considered as ‘low-risk-but-not-no-risk’ symptoms [17]. Studies indicate that patients presenting these symptoms may have a longer diagnostic interval and progress into advanced cancer stages [18–22]. It is a challenge for the GP to identify the few CRC cases among all the patients with similar symptoms, but without CRC. However, a recent study has shown that CRC patients tend to see their GP more often and have more tests performed than the average patient in the year preceding a CRC diagnosis [23]. This may indicate a potential diagnostic window for early identification of patients with CRC. Thus, tools that can assist the GP in the diagnostic workup of patients presenting with uncharacteristic symptoms of CRC are highly needed.

Immunochemical Faecal Occult Blood Test (iFOBT) may be one solution to the problem. Unlike the guaiac faecal occult blood test (gFOBT), which requires three tests, the iFOBT requires only one test and no pre-test dietary restrictions are needed as the test uses antibodies specific to human globin [24]. Furthermore, studies have found iFOBT to be diagnostically superior to gFOBT [25, 26]. The diagnostic performance of iFOBT has mainly been investigated in relation to screening. In these studies, the sensitivity of iFOBT has generally been found to be 80–90 %, the specificity to be above 90 % and the PPV to be better than for most alarm symptoms (10 %) [26–30]. Only few recent small-scale studies have investigated the use of iFOBT on symptomatic patients, and these findings suggest that iFOBT could be beneficial as a case-finding tool in the detection of CRC in general practice [31–37]. No study has focused on the use of iFOBT in patients presenting with non-alarm symptoms of CRC. Large-scale controlled studies are needed to investigate if and how iFOBT can be used in the diagnostic workup of symptomatic patients in primary care. This paper presents a study that implements iFOBT as a diagnostic tool in general practice in individuals presenting with non-alarm symptoms of CRC.

## Methods/Design

### Aim

The aims of the study are to:Evaluate the uptake and clinical use of iFOBT in general practice after targeted courses for GPs in correct use of the test.Estimate the diagnostic value of iFOBT when used on patients presenting with non-alarm symptoms of CRC.Investigate the clinical implications of using iFOBT for case finding in general practice.

### Setting and study population

The study will be performed in the Central Denmark Region (CDR), which is one of five regions in Denmark. The CDR covers approx. 1.2 million inhabitants, 381 general practices, 836 GPs and 19 municipalities. In each municipality, the GPs are organised in units (except for the GPs in the island municipality of Samsø that are included in the unit of Aarhus). Each unit is headed by a chairman who represents the GPs of the municipality. The GPs in Denmark own their own clinic, and approx. 1550 persons are listed per GP. Clinics operate as either solo practices or partnership practices. Remuneration is based on a mix of capitation (25 %) and fee-for-service (75 %) based on a centrally negotiated collective agreement. The GP acts as a gatekeeper to specialised care in the secondary sector, and the citizens must contact the GP for medical advice unless in case of emergency. Approx. 10–20 % of all consultations in general practice ends up with a referral [38]. Nearly all citizens (99 %) are listed with a specific general practice, and the GP is remunerated on the basis of a contract with Danish Regions and must fulfil certain requirements for waiting time and access. iFOBT is available to Danish GPs only to a limited extent as part of the urgent referral for non-specific serious symptoms that might be cancer [39]. However, no logistic setup is available in general practice regarding ordering and analysing the test.

The study population constitutes the 836 GPs in the 381 general practices in the CDR and the individuals aged 30 years or more who are listed with these practices.

### Design

The study uses a cluster-randomised stepped-wedge design [40]. This design allows us to roll out the study in large scale and to include all general practices in the CDR.

During the first seven months of the study period, each municipality and their appertaining GPs will be randomly and stepwise included in the study to receive intervention (Fig. 1). The intervention (see details later) consists of sending iFOBT kits and a clinical guideline to the GPs and to offer an optional continuous medical education (CME) session about CRC diagnosis. The invitation to the CME is sent to the chairman of the GP unit who will arrange the date and time of the meeting. The month in which the CME is arranged determines the date of inclusion for each municipality. Thus, the date at which a municipality is included is defined as the first working day of the month in which the CME is planned to be conducted. As the CME component is optional, the GP units can choose not to participate in the CME. These municipalities are included on the first working day in the month after confirmation of non-participation (Fig. 2). The specific date of the CME is flexibly arranged as the CME can be scheduled to take place on any of the first 7 months, depending on the preferences of the GPs in the municipality (in consideration of other arrangements targeting GPs in the municipality, availability of venue, etc.).

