### Randomisation

The study uses cluster randomisation. The 19 municipalities in the CDR are randomly allocated to monthly starts of the intervention, ensuring that all municipalities are included within 7 months. The randomisation is performed prior to initiation of the study and determines when each cluster is offered to participate in the CME. The randomisation is blinded to the research group and is manually performed by two research fellows with no connection to the project.

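### Randomisation sets when the CME is offered, but the GP unit's own scheduling sets when a municipality crosses over, which weakens (recoverably) the randomised comparison of colonoscopies and urgent referrals

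*Protocol article*

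**What the plan says.** All references are to the protocol article.

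**Start described as random.** The Randomisation section says the municipalities "are randomly allocated to monthly starts of the intervention". The Design section and the Fig. 1 caption likewise describe random inclusion over seven possible dates.

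**Start as operated.** The Randomisation section adds that the draw "determines when each cluster is offered to participate in the CME". The Design section then passes control to the cluster: "The invitation to the CME is sent to the chairman of the GP unit who will arrange the date and time of the meeting". The timing is open, since "the CME can be scheduled to take place on any of the first 7 months, depending on the preferences of the GPs in the municipality". The inclusion date follows from it: "The month in which the CME is arranged determines the date of inclusion for each municipality". For units that decline: "These municipalities are included on the first working day in the month after confirmation of non-participation".

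**Use in the analysis.** Under Statistical analysis, a practice counts as control up to the point at which it crosses over. The part on clinical implications estimates colonoscopies and urgent referrals before and after intervention. It compares the number and stage of CRCs with those diagnosed before the test was introduced in general practice. The article mentions no analysis by randomised month.

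**The concern.** In a stepped wedge, exposure rises with calendar time by construction. The comparison is protected because the order of crossover is drawn at random and is therefore independent of how each cluster's outcomes were moving anyway. Here the random draw sets the offer, and a second step controlled by the cluster sets the crossover. The Design section gives other local arrangements for GPs and venue availability as reasons for flexibility. Whether such reasons, or others, go together with local trends in referral and colonoscopy is unknown.

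If they do, cluster and month effects in the model will not remove the problem, because they absorb level differences and shared time trends but not trends that differ between early and late units. At stake is whether the estimated change in colonoscopies and urgent referrals can be read as a randomised effect.

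**Working it through.** **No stated figure depends on this point.** The sample-size section gives 33,600 × 0.10 × 0.10 = 336 CRCs and a detectable fall in stage IV from 25% to 16%. Neither contains a crossover or cluster term, so they neither support nor refute the point. The textual finding rests on setting the sections side by side, as above. The arithmetic below only shows what could follow.

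**Possible shift.** An offer in month 1 with a CME in month 7 is a delay of 7 − 1 = 6 months.

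**Illustration.**
- From the document: 12 months, 7 start months, and 18 units that can schedule separately (19 municipalities, with the GPs of Samsø placed in the Aarhus unit).
- Assumed: unit i has a monthly log-rate trend sᵢ with mean 0 and SD 1% or 2%. The true effect is 0. A CME cannot be held before it is offered, so actual month aᵢ = offer month oᵢ + delay dᵢ, with 0 ≤ dᵢ ≤ 7 − oᵢ.
- Estimator with unit and month effects: β = Σ x̃ᵢₜ yᵢₜ / Σ x̃ᵢₜ², where x̃ᵢₜ = xᵢₜ − x̄ᵢ − x̄ₜ + x̄, xᵢₜ is exposure and yᵢₜ = sᵢt.

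Absolute bias in the log rate ratio (6,000 runs per cell):

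| How delay arises | Correlation of start with trend | Coded by actual month, SD 1% / 2% | Coded by offer month |
|---|---|---|---|
| No delay | 0 | about 0 | about 0 |
| Delay unrelated to trend | 0 | about 0 | about 0 |
| Units with below-median trend delay at random | about −0.33 | 0.023 / 0.045 | about 0 |
| Delay set wholly by trend rank | about −0.65 | 0.034 / 0.067 | about 0 |

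On the ratio scale, 0.02 to 0.07 is exp(0.02) = 1.02 to exp(0.07) = 1.07, a spurious change of about 2-7%. The sign reverses if the assumed link between trend and delay is reversed.

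**Dilution when exposure is coded by offer month.** The share of a constant effect that is kept is κ = Σ x̃(o) x(a) / Σ x̃(o)². Delay is unrelated to trend and capped at month 7.

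| Delay | Mean delay (months) | Effect kept |
|---|---|---|
| 0-1 month | 0.44 | about 75% |
| 0-2 months | 0.85 | about 56% |
| Uniform over the remaining months | 1.67 | about 33-34% |

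Check on the means: two of the 18 units are offered in month 7 and cannot delay, so the first is 16/18 × 0.5 = 0.44. With three units in each of months 1-4 and two in each of months 5-7, the mean room is [3(6+5+4+3) + 2(2+1+0)]/18 = 60/18 = 3.33 months, and half of that is 1.67.

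**The case against.** **The offer month is still random.** A reader might infer that the start is purely self-chosen and randomisation is lost. The document does not support that. The offer is randomised and, if no CME precedes its offer, it sets the earliest possible crossover. Start order therefore cannot be fully correlated with trend: even delay driven entirely by trend rank gave about −0.65. Biases of 0.07-0.14, which need full correlation, are not attainable under this rule. This part of the objection stands.

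**Delay may be innocent.** Venue and calendar conflicts need have nothing to do with referral trends, and then either coding is unbiased. This stands too. It makes the bias possible, not shown.

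**Reach is limited.** A reader might take every outcome to be affected. Uptake and PPV have no control period. CRC number and stage may be meant as a historical comparison, which self-chosen months would affect little.

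**The analysis plan is not shown.** Coding by offer month and a table of assigned against actual dates could sit there, and the Fig. 2 flowchart could limit rescheduling. This does not remove the point. The inclusion rule and the definition of control time are stated in the article, they conflict with its account of random starts, and the figure captions do not settle the conflict.

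**Samsø.** That its GPs "that are included in the unit of Aarhus" leaves 18 units, not 19, to schedule independently. It alters no stated figure and adds no weight here.

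**Conclusion.** The point holds in a limited form. The article calls the start month random, but its rule lets the GP unit set the actual crossover after the random offer, and control time ends at that crossover. The protection of randomisation is weakened, not destroyed, for the before/after comparison of colonoscopies and urgent referrals. CRC number and stage are affected only if they are also analysed by crossover date.

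The illustrative range of 0.02-0.07 rests on trend SDs and delay mechanisms that are assumptions, not figures from the document. It shows that bias can arise, not that it will. Coding by the randomised offer month removes the bias in every scenario tried, at a price in dilution that is large exactly where delays are long.

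**What to change.** **Preferred.** Reconcile the Design section with the Randomisation section and Fig. 1 by tying the mandatory starting package to the first working day of the randomised month, whatever the unit decides about the CME. Only the optional CME date then floats. This is workable because units that decline already receive the package without a meeting. Table 1, which places the CME within a month of inclusion, must be changed to match.

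Cost: this alters the delivery of the intervention as well as its wording. Some units would hold kits before their CME, possibly by months (up to 6 for an offer in month 1 and a CME in month 7).

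**If roll-out can no longer change.** For colonoscopies and urgent referrals, and for CRC number and stage if analysed by crossover date:
- make exposure by randomised offer month the main, intention-to-treat analysis;
- report exposure by actual inclusion month as a sensitivity analysis;
- tabulate assigned against actual month for every unit;
- state that the main estimate may be substantially diluted if delays are long.

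Cost: no new data beyond the two dates per unit, but a loss of effect size, and so of power, that grows with delay.

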**Fig. 1 Fig1:**
[figure not shown]
Stepped-wedge design used for the study. Most municipalities start out as usual care (C). Within the first seven months, all will cross over to intervention (I). Seven possible dates of inclusion are available; the 19 municipalities are randomly distributed between these

**Fig. 2 Fig2:**
[figure not shown]
Flowchart of inclusion date for the participating municipalities

### Randomisation

The study uses cluster randomisation. The 19 municipalities in the CDR are randomly allocated to monthly starts of the intervention, ensuring that all municipalities are included within 7 months. The randomisation is performed prior to initiation of the study and determines when each cluster is offered to participate in the CME. The randomisation is blinded to the research group and is manually performed by two research fellows with no connection to the project.

### Intervention

The intervention was developed using the behavioural change wheel as analytical framework to identify potential barriers in the study and to target the intervention towards specific subjects [41]. Before implementing the intervention in large scale, we tested and optimised the intervention in a pilot study among seven general practices to ensure optimal fit with the GPs’ daily clinical practice. The process evaluation followed the recommendations provided by the Medical Research Council (MRC) for evaluation of complex interventions [42]. A detailed description of the pilot study will be published in a separate article.

The intervention consists of a mandatory intervention (for all GPs) and an optional intervention (for GPs that participate in the CME) (Table 1).

**Table 1 Tab1:** Intervention used in the study; a mandatory component for all GPs and an optional component

	Content	Time
Mandatory intervention	Starting package:	Date of inclusion
	10 iFOBT kits	
	Clinical instruction on iFOBT use in general practice	
	Online educational material	Date of inclusion
	Mail with iFOBT status	Approx. one month after inclusion
Optional intervention	Continuous medical education (CME)	During the first month of inclusion

#### Mandatory intervention

On the date of inclusion, each GP in the included municipality receives a starting package consisting of 10 iFOBT kits and a clinical instruction on iFOBT use in general practice and how to order the test through the online WebReq system. Furthermore, educational material on CRC diagnostics and use of iFOBT will be available on a web page announcing relevant news for GPs (www.praksis.dk). The online material will have links to the slides from the CME PowerPoint presentation, the clinical instruction and images of the contents in the iFOBT kits.

Approx. 1 month after inclusion, participating GPs will receive a mail containing: status on number of tests requested from their municipality, number and rate of positive tests, number of general practices in the municipality that have started using the test and status of the total number of iFOBTs requested in the CDR. Furthermore, information on how to get help to get started is provided.

#### Optional CME intervention

The CME consist of a 45–60 min lecture on CRC diagnostics and use of iFOBT in general practice (Table 2). The CME is an interactive lecture with cases, discussion and questions based on international literature and guidelines and adapted to a Danish general practice setting. GPs attending the meeting will be registered to facilitate suitable grouping of CME-attending general practices.

**Table 2 Tab2:** Programme of the continuous medical education (CME) of approx. 45–60 min

Welcome
• Introduction of presenters
• Brief introduction to the rational of the study
Presentation, part one: Diagnostics of colorectal cancer in primary care
• Case story
• Update on diagnostics of CRC in today’s general practice
• Why is it important to diagnose CRC in early stages?
Presentation, part two: iFOBT in general practice
• Rational use of iFOBT in general practice
• Indications for using iFOBT
• Actions on test result
• Requesting the test and logistic setup of the study
Questions/discussion
Concluding remarks

### Clinical instruction on iFOBT use in general practice

A clinical instruction was developed for the study (Table 3). The instruction contains suggested indications for using the iFOBT and recommended actions on positive and negative test results. It is aimed for individuals of 30 years or above with symptoms and signs that could be related to CRC. However, iFOBT should not be used on patients presenting alarm symptoms that justify urgent referral to the cancer patient pathway (CPP) [39]. The content is based on published literature.

**Table 3 Tab3:** Instructions for using iFOBT in general practice (not exhaustive, other indications are possible)

Overall indication	Individuals aged ≥ 30 years with symptoms and signs of colorectal cancer, but do not fulfill the criteria of referral in the CPP
Typical indications	Change in bowel habits^a^
	Abdominal pain^a^
	Anemia or decrease in hemoglobin >10 %^a^
	Diagnostic workup of patients with IBS
	Non-specific symptoms (weight-loss, fatigue, loss of appetite)^b^
Actions on test result	Positive test (≥50 μg/L)
	30–39 years: Referral to colonoscopy with remark of blood in stools found by iFOBT.
	≥40 years: Urgent referral in the cancer patient pathway for colorectal cancer.
	Negative test (≤49 μg/L)
	Colorectal cancer cannot be excluded.

^a^Not eligible for urgent referral in the CPP for CRC

^b^Not eligible for urgent referral in the CPP for non-specific serious symptoms

